## Abstract

**Background:**

The incidence of preadolescent acne among women is increasing. Acne deteriorates the quality of life; conventional treatment options are limited and have not been effective against acne, particularly acne associated with menstruation. Despite evidence that acne associated with menstruation abnormalities naturally improves when menstruation recovers to normal, there have only been few studies on the effects of dysmenorrhea treatment on acne. Therefore- we designed this study to assess the effects of gyejibokryung-hwan (GBH) and dangguijagyag-san (DJS), which are widely used in dysmenorrhea treatment, on acne associated with menstruation cycle.

**Methods:**

This is a protocol for a randomized, double-blind, parallel-group, placebo-controlled and multicenter trial. One hundred and sixteen participants with dysmenorrhea accompanied by acne vulgaris will be recruited at three centers and randomized into two groups, the herbal treatment group and placebo group. The participants will receive GBH or DJS based on pattern identification or placebo granules thrice daily for 8 weeks, with an 8-week follow up. The primary outcome will be the mean percentage change in the count of inflammatory acne lesions. The secondary outcomes would be based on dysmenorrhea numeric rating scale, verbal multidimensional scoring system for dysmenorrhea, acne numeric rating scale, investigator’s static global assessment scale of facial acne vulgaris, and safety testing. Adverse events will also be reported.

**Discussion:**

The effects of GBH or DJS used in dysmenorrhea treatment on acne associated with the menstrual cycle will be evaluated. The findings of this trial will provide evidence regarding the effect of herbal medicine in improving acne vulgaris associated with menstruation in women.

**Trial registration:**

Korean Clinical Trial Registry (http://cris.nih.go.kr; registration number: KCT0002259). Date of registration: March 10, 2017

## Background

Acne is a chronic inflammatory skin disease of the pilosebaceous unit. The primary causes of acne include increased sebum secretion, follicular hyperkeratinization, *Propionibacterium acnes* within the follicle, and inflammatory responses [1]. Acne is considered an adolescent affection, but over the last few years, adult acne have been increased [2–4]. Postadolescent acne appears to occur more frequently in women than in men [5, 6]. The unique features of adult acne in women are that it is related to the menstrual cycle [3, 7]. Up to 78% of women with acne have premenstrual flares [3]. Accumulation of sebum within the sebaceous glands due to changes in sex hormone secretion during ovulation and menstruation has been proposed as a potential contributor to premenstrual acne [8, 9]; however, the mechanism underlying this phenomenon remains unknown.

Because adult acne in women is associated with menstrual-related hormones, it is usually accompanied by menstrual abnormalities, i.e. dysmenorrhea. Primary dysmenorrhea is defined as pain during menstruation in the absence of pelvic problems [10–12]. The prevalence of dysmenorrhea varies from 16 to 83% in women of reproductive age [10, 13]. Oral contraceptives are used to treat dysmenorrhea [11] and administered to female patients with acne who do not respond to medication and are suspected of having hormonal abnormalities [14, 15]. But the actual frequency of prescribing oral contraceptives is low because of possible side effects such as nausea, vomiting, and weight gain and social conventions against single female patients consuming oral contraceptives.

In traditional Chinese medicine and traditional Korean medicine (TKM), blood stagnation during ovulation and menstruation is considered the cause of dysmenorrhea [16, 17] and aggravated acne associated with the menstrual cycle. Therefore, treatment with herbal medicine for dysmenorrhea often improves symptoms of acne associated with the menstrual cycle; however, no study on this has been conducted thus far. Gyejibokryung-hwan (GBH) and dangguijagyag-san (DJS), administered in this trial, have been long used in East Asian countries for treatment of dysmenorrhea [16, 18, 19]. The effects of GBH and DJS on dysmenorrhea have been investigated [16, 18, 19]. The prescription of the two herbal medicines is usually determined by a physical state diagnosis according to TKM patterns [16, 17]. Excess-deficiency pattern for dysmenorrhea is importantly considered. In general, GBH is used for the excess pattern of dysmenorrhea and DJS for deficiency pattern of dysmenorrhea. Administration based on the pattern improves clinical results; therefore, we aimed to reflect the clinical condition to the research.

The objective of this trial was to determine whether the herbal medicines prescribed to treat dysmenorrhoea based on the pattern could simultaneously improve acne vulgaris associated with the menstrual cycle.

## Methods / Design

### Objective

To investigate the effects of GBH and DJS on acne vulgaris in patients who were administered these herbal medicines for dysmenorrheal treatment.

### Hypothesis

The primary objective is to investigate whether herbal medicine treatment for dysmenorrhea can reduce the number of acne vulgaris lesions in comparison with that reported with placebo treatment. The primary null hypothesis is as follows: Eight-week GBH and DJS treatment does result in any change in the number of acne vulgaris lesions between the treatment group and placebo group.

### Design

This study is a randomized, placebo-controlled, double-blind, parallel-group and multicenter trial. The flow chart of the study has been presented in Fig. 1.

**Fig. 1 Fig1:**
[figure not shown]
Study flow chart

### Ethics

The protocol design is in accordance with the Declaration of Helsinki and Korean Good Clinical Practice Guidelines. This trial is authorized by the Institutional Review Board of the Kyung Hee University Korean Medicine Hospital (approval number: KOMCIRB-161014-HR-053), Kyung Hee University Korean Medicine Hospital at Gangdong (approval number: KHNMCOH2016–10–003-003) and Woosuk University Korean Medicine Medical Center (approval number: WSOH IRB 1703–02). Signed informed consent forms will be obtained from all eligible participants before enrollment. This trial is registered with the Korean Clinical Trial Registry (CRIS), Republic of Korea: KCT0002259.

### Participants

#### Diagnostic criteria for excess and deficiency patterns in TKM

A doctor practicing Korean medicine will judge excess and deficiency patterns of dysmenorrhea based on chief physical signs: color of lower eyelid, facial complexion, tongue diagnosis, abdominal examination, and hot flush [20].

Deficiency patterns of dysmenorrhea may comprise pale lower eyelid, pale white complexion, pale tongue, weak abdominal tension and not existing or slightly existing of the feeling of heat up, respectively. Excess patterns of dysmenorrhea may comprise normal or red colored lower eyelid, darkish complexion, red tongue, tight and strong abdominal tension, presence of hot flush.

#### Inclusion criteria

Women older than 19 years and of childbearing agePatients who have more than 10 inflammatory acne lesions on their facePatients who have menstrual pain score of more than grade 1 according to the verbal multidimensional scoring system (VMSS)Patients who had regular menstrual cycle of 23–33 days in the last 3 monthsPatients in who acne vulgaris related to the menstrual cycle aggravatedWritten informed consent

#### Exclusion criteria

Patients who consumed the following medicines:Topical or systemic corticosteroids (in the last 1 month)Herbal medicine for acne treatment (in the last 1 month)Nonsteroidal anti-inflammatory drugs (NSAIDs) (in the last 2 weeks)Oral contraceptives (in the last 1 month)Topical or oral vitamin A derivatives (in the last 1 month)Antibiotics (in the last 1 month)Other unsuitable drugs as judged by the investigators
Body Mass Index (BMI) <19 or BMI ≥ 25Liver function abnormality [aspartate aminotransferase (AST) or alanine aminotransferase (ALT) ≥ 60 IU/L] or renal function abnormality [blood urea nitrogen (BUN) ≥ 30 mg/dL or a serum creatinine levels ≥1.5 mg/dL]Pregnancy or breastfeeding or planning to conceive [human chorionic gonadotropin (hCG)-positive women]Patients who have malignant tumor, serious infection, or severe systemic diseasesPatients who participated in other clinical trials in the last 3 monthsUnsuitability as judged by the investigators

#### Rejection and withdrawal criteria

Use of forbidden drugs, such as topical or systemic corticosteroids, herbal medicine, oral contraceptives, topical or oral vitamin A derivatives and antibioticsTreatment that might influence the results of the trial without the agreement of a researcherVoluntary withdrawal from the trialParticipants who have skin rash, flare or itching during the trialParticipants not following the protocol, or taking <80% of the prescribed dosesParticipants who have anorexia, vomiting, nausea or diarrhea after taking the drug

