#### Primary outcomes

Primary outcome will be presented as the mean percentage change in total lesion counts from baseline to the end of the treatment. Total lesion counts refer to the sum of the inflammatory and non-inflammatory lesions. Inflammatory lesions included inflammatory papules, pustules, and cysts and non-inflammatory lesions include black and white head comedones. The front and both sides of each participant’s face will be photographed on each visit using a Lumix-LX2 digital camera (Panasonic, Osaka, Japan). Two Korean medicine doctors who have been in clinical practice for more than 3 years will count the lesions independently. Discrepancies will be resolved by discussion with a third researcher.

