#### Patient groups for data analysis

##### Intent-to-treat population

The ITT population will include all participants treated with at least one dose of the study drug. If the patients dropped out during the trial or if there is missing data, the “last observation carried forward” principle will be used to compensate for that data.

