##### Per-protocol population

The per-protocol population will include patients who would consume more than 80% of the prescribed doses of the study drug and complete the trial.

Effectiveness will be evaluated by ITT principle and per-protocol principle. When analysis results are different, the ITT principle will be considered for the main analysis and subordinately, we will compare the results of the analysis based on the per-protocol principle. Demographic and safety test will be analyzed by ITT principle and the data for safety test will be used without adjustment.

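### Withdrawal for low intake, protocol deviation, prohibited drugs or listed reactions, with no provision for continued lesion counts, can leave the ITT analysis with carried-forward instead of observed week-8 counts

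*Protocol article*

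**What the plan says.** The section Rejection and withdrawal criteria is a single list. It contains use of forbidden drugs, voluntary departure from the trial, skin rash, flare or itching, women "not following the protocol, or taking <80% of the prescribed" doses, and women with "anorexia, vomiting, nausea or diarrhea after taking the drug". No severity threshold is attached to the reactions, and nothing separates stopping the granules from leaving the study.

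The analysis sections then state:
- Intent-to-treat population: "The ITT population will include all participants treated with at least one dose of the study drug". The imputation rule applies "If the patients dropped out during the trial or if there is missing data", and the method is "last observation carried forward" (LOCF).
- Per-protocol population: women who "consume more than 80% of the prescribed doses of the study drug and complete the trial". If the two analyses disagree, "the ITT principle will be considered for the main analysis".
- Primary outcomes: the endpoint is the "mean percentage change in total lesion counts from baseline to the end of the treatment", that is, week 8.

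Table 1 schedules photographs and lesion counts at every visit up to visit 6 (week 8), compliance checks at visits 3 to 6, and the pain and acne rating scales through week 16. No section says that a woman who meets a withdrawal criterion is still photographed or counted.

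**The concern.** Low intake, protocol deviation, prohibited drug use and reactions to the granules all happen after randomisation. They may depend on the assigned treatment or on how the skin is responding. An ITT analysis is meant to keep such women with the outcomes they actually had. If meeting a criterion ends their assessments, their week-8 counts are lost and an earlier count stands in.

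Two consequences follow. The women with an observed week-8 count come close to the per-protocol set, because the withdrawal rule and the per-protocol rule use the same 80% cut-off. The ITT result is then a less independent check on the per-protocol result than it appears. Also, if more women are withdrawn in one arm, LOCF can shift the treatment contrast. A count that was never taken cannot be recovered at the analysis stage, whatever imputation method is used.

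**Working it through.** **Reading the sections together**

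1. The adherence, prohibited-drug and reaction items share one list and one heading with voluntary departure from the trial. The natural reading is that all have the same consequence.
2. The ITT section provides LOCF for those who drop out. No other section provides for continued counts.
3. So a woman withdrawn before week 8 stays in the ITT set (one dose is enough), but only through her last earlier count.
4. There is an exception. Total intake over 8 weeks is final only at visit 6, when the week-8 photograph is also due. A woman found below 80% only then may already have her primary outcome.

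**Illustrating the size**

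The article gives no withdrawal rate by arm and no expected percentage improvement, so the plan has no bias figure to reproduce. Its only related figure is the 15% dropout in Sample size calculation: 0.15 × 116 = 17.4 women.

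Assumed inputs:
- Withdrawn: 20% on active, 10% on placebo. With 58 per arm this is 11.6 + 5.8 = 17.4, which matches 15% overall. The split between arms is an assumption.
- True week-8 improvement: 40% against 20%, or 30% in both arms for the null case.
- Linear improvement, so the fraction reached at the last count is f = week/8: 0.25 at week 2 and 0.75 at week 6.
- A withdrawn woman, if counted at week 8, would have shown her arm's mean.

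For an arm with true mean μ and withdrawn share w:

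LOCF mean = (1 − w)μ + w·f·μ

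| Case | Last count | Active | Placebo | Difference |
|---|---|---|---|---|
| 40% vs 20% | week 2 | 0.8×40 + 0.2×10 = 34 | 0.9×20 + 0.1×5 = 18.5 | 15.5 (true 20) |
| 40% vs 20% | week 6 | 0.8×40 + 0.2×30 = 38 | 0.9×20 + 0.1×15 = 19.5 | 18.5 (true 20) |
| 30% vs 30% | week 2 | 0.8×30 + 0.2×7.5 = 25.5 | 0.9×30 + 0.1×7.5 = 27.75 | −2.25 (true 0) |
| 30% vs 30% | week 6 | 0.8×30 + 0.2×22.5 = 28.5 | 0.9×30 + 0.1×22.5 = 29.25 | −0.75 (true 0) |

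The shift equals −(1 − f)(w_A·μ_A − w_P·μ_P), with A for active and P for placebo. With equal means and equal withdrawal it is zero. If withdrawal were higher on placebo, the null shift would change sign.

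**The case against.** The strongest reply is that the article never says visits stop. Only one item in the list names the trial as what is being left, and a condensed article may leave the handling of withdrawn women to the full protocol. It stands that the end of follow-up is an inference. But the inference rests on what is printed: one undivided withdrawal list, LOCF for dropouts, and no provision for continued counts. If the full protocol keeps these women under observation, one sentence resolves the point.

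Second, the per-protocol definition asks for adequate intake as well as completion, and the plan foresees that the two analyses may differ. Both suggest that some women below 80% remain to the end. No text applies the 80% cut-off at interim visits. This stands, and it weakens the point most for the adherence item. It does not help women withdrawn before week 8 for reactions or prohibited drugs.

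Third, the size depends on the scenario. This stands too: later withdrawal makes the shift small. With higher withdrawal assumed on active, the bias goes against the herbal arm, so it would not create a false claim of superiority. What is calculated is LOCF bias, and it should not be counted a second time if LOCF is criticised separately.

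Fourth, counts taken after prohibited acne drugs partly measure those drugs. That is a real cost of continued follow-up, though it is what an ITT comparison accepts.

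**Conclusion.** The point holds in a limited form. Followed as written, the criteria can remove week-8 counts for post-randomisation reasons that may be related to treatment. The ITT analysis then moves closer to per-protocol plus imputation and can be biased if withdrawal differs by arm. Under the stated assumptions a true 20-point difference falls to between 15.5 and 18.5, and a true null shifts by −2.25 to −0.75 points against active. These figures show direction and order of size only. They rest on an assumed split of withdrawals, linear improvement, and arm-average outcomes in withdrawn women.

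A reader might infer more than the documents support:
- That ITT simply becomes per-protocol plus imputation, or that the difference between the two disappears. Women found below 80% at visit 6 may have an observed count, and a woman who reaches week 8 but misses later visits may be outside per-protocol yet observed.
- That the listed reactions are common. The article gives no frequencies.
- That women are withdrawn because their acne worsens. In the list, flare stands between rash and itching and may well mean a skin reaction.
- That 15.5 is the expected result. It belongs to the earliest post-baseline count; 18.5 is equally compatible with the text.

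**What to change.** Divide the section into two parts. The first holds reasons to stop study product, left to the clinical team and unchanged here. The second is withdrawal from the trial, meaning withdrawal of consent.

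Then state that:
- women who stop product, take less than 80% or use prohibited drugs continue, where they consent, with the photographs scheduled to week 8 and the questionnaires scheduled to week 8 and through follow-up;
- their observed counts enter the ITT analysis, so that imputation covers only counts that are truly missing;
- intake below 80% is a per-protocol exclusion and nothing more.

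This is a short amendment, and it adds no visit that is not already in Table 1. It costs some retention effort. Counts after prohibited acne drugs will also reflect those drugs, which gives a treatment-policy estimate consistent with the stated ITT principle. The per-protocol analysis remains as the comparison. The change helps only while women are still in follow-up.

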### Recruitment

Through advertisements and referrals, a total of 116 patients with dysmenorrhea accompanied with acne vulgaris will be recruited at the Kyung Hee University Korean Medicine Hospital, Kyung Hee University Korean Medicine Hospital at Gangdong and Woosuk University Korean Medicine Medical Center.

### Randomization and concealment

Random numbers will be generated by stratified block randomization in random block of 4, and the 116 patients will be randomly allocated in a 1:1 ratio to herbal treatment group or the placebo control. An independent statistician who is unaware of the design and purpose of the study will generate a randomization table using SAS software for Microsoft window (version 9.1.3; SAS Institute Inc., NC, Cary, USA). The statistician will keep the randomization lists and inform the researcher of the matching cord number either by text message or via mobile communication application.

Eligible participants will be screened using inclusion/exclusion criteria and the participants who meet the criteria will be included in the trial. After signing the informed consent form, the patients will be randomly allocated to the two groups.

### Blinding

Participants, investigators, and the clinical trial pharmacist will be blinded to the treatment allocation throughout the course of the study. The statistician will uncover the blinding when necessary, such as on occurrence of a serious adverse event (SAE). The researcher has to inform the statistician when the blinding has to be uncovered. After the confirmation and approval about the reason for cord break, the procedure for uncovering the blinding will begin.

### Interventions

#### GBH and DJS

The experimental group will be administered GBH or DJS granules according to the excess or deficiency pattern identification. The excess pattern group for dysmenorrhea will be orally administered GBH granules (3 g/pouch) thrice daily before or between each meal for 8 weeks. The deficiency pattern group for dysmenorrhea will be administered DJS granules (3 g/pouch) thrice daily before or between each meal for 8 weeks.

The GBH and DJS granules were manufactured by Hanpoong Pharm & Food Co. Ltd. (Jeonju, Republic of Korea) in line with Korea Good Manufacturing Practice authorization. Both GBH and DJS were approved by the Korean Ministry of Food and Drug Safety. GBH and DJS contain 3 g (dry weight) of water-extracted granules combined with lactose and starch. GBH is composed of 5 herbs: Cinnamomi Ramulus (*Cinnamomum cassia* Presl, family Lauraceae; 1.33 g), Poria Sclerotium (*Poria cocos* Wolf, family Polyporaceae; 1.33 g), Moutan Radicis Cortex (*Paeonia suffruticosa* Andrews, family Paeoniaceae; 1.33 g), Persicae Semen (*Prunus persica* Batsch or *Prunus davidiana* Franchet, family Rosaceae; 1.33 g), Paeoniae Radix (*Paeonia lactiflora* Pallas, family Paeoniaceae; 1.33 g). DJS is composed of 6 herbs: Angelicae Gigantis Radix (*Angelica gigas* Nakai*,* family Umbelliferae; 1.00 g), Cnidii Rhizoma (*Cnidium officinale* Makino or *Ligusticum chuanxiong* Hort. family Umbelliferae; 1.00 g), Paeoniae Radix (*Paeonia lactiflora* Pallas, family Paeoniaceae; 2.00 g), Poria Sclerotium (*Poria cocos* Wolf, family Polyporaceae; 1.33 g), Atractylodis Rhizoma Alba (*Atractylodes japonica* Koidzumi or *Atractylodes macrocephala* Koidzumi, family Compositae; 1.33 g), Alismatis Rhizoma (*Alisma orientale* Juzepzuk, family Alismataceae; 1.67 g). Voucher specimens will be reserved at the research library of Hanpoong Pharm & Food Company.

#### Placebo

The placebo group will receive the placebo, which does not contain any active ingredients, but is similar in appearance, taste, and aroma to the GBH or DJS granules. Placebo will be orally taken (3 g/pouch) thrice daily before or between each meal for 8 weeks. The excess pattern group for dysmenorrhea will receive the GBH placebo and the deficiency pattern group for dysmenorrhea will receive DJS placebo.

The placebo was also manufactured by Hanpoong Pharm & Food Co. Ltd. (Jeonju, Republic of Korea), following the placebo guidelines of the Korean Ministry of Food and Drug Safety. All products were packaged by Hanpoong Pharm & Food Co. Ltd.. Either 45 GBH or DJS or placebo pouches will be provided to each randomized participant every two weeks, at visit 2 (week 0) to visit 6 (week 8).

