### Outcomes

The detailed outcome measurement time points are provided in Table 1.

**Table 1 Tab1:** Study process treatment and outcome measurements

Activity	Visit 1	Visit 2	Visit 3	Visit 4	Visit 5	Visit 6	Visit 7	Visit 8
Time Schedule	Week 1	Baseline	Week 2	Week 4	Week 6	Week 8	Week 12	Week 16
Window visit		±3 days	±3 days	±3 days	±3 days	±3 days	±3 days	±3 days
Demographic information-taking	X							
Informed consent form	X							
General medical history-taking	X							
Photographing the patient’s face Count of inflammatory/non-inflammatory lesions	X	X	X	X	X	X		
Blood tests (liver function test, renal function test)	X					X		
Blood tests		X				X		
Urine pregnancy test	X					X		
Randomization & allocation		X						
Investigational Produce		X	X	X	X			
Numeric rating scale (menstrual pain)		X		X		X	X	X
Verbal multidemensional scoring system grade	X	X		X		X	X	X
Investigator’s Static Global Assessment Scale of Facial Acne Vulgaris		X	X	X	X	X		
Numeric rating scale (acne)		X	X	X	X	X	X	X
Monitoring adverse events			X	X	X	X	X	X
Compliance check			X	X	X	X		
Blinding check						X		

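### The dispensing text names visits 2 to 6 (five supplies) but Table 1 marks visits 2 to 5 (four), leaving one 15-day supply at the end-of-treatment visit in dispute

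*Protocol article*

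**What the plan says.** The protocol article states the dispensing schedule twice.

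- **Interventions, Placebo.** The last paragraph covers both arms: "Either 45 GBH or DJS or placebo pouches will be provided to each randomized participant". The timing follows at once: "every two weeks, at visit 2 (week 0) to visit 6 (week 8". Visit number and week are given at both ends of the range.
- **Outcomes, Table 1.** The row labelled "Investigational Produce" is marked at visits 2, 3, 4 and 5 (baseline and weeks 2, 4 and 6). It is blank at visit 6 (week 8) and after.

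The treatment period is stated consistently. The GBH and DJS section has the product taken "thrice daily before or between each meal for 8 weeks", and the Placebo section matches it: "Placebo will be orally taken (3 g/pouch) thrice daily before or between each meal for 8 weeks". The Methods paragraph of the abstract adds the period after treatment: "placebo granules thrice daily for 8 weeks, with an 8-week follow up". The Acne vulgaris subsection of the secondary outcomes puts the end of treatment at 8 weeks, which is visit 6.

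**The concern.** A site that works from the Placebo section would hand out a fifth supply on the day treatment is due to end. A site that works from Table 1 would not. Three centres are recruiting, so practice could differ between them.

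Three features of the schedule make the disputed supply matter:

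- **No later count.** Table 1 has compliance checks at visits 3 to 6 and none afterwards, so pouches issued at visit 6 would have no scheduled count.
- **No later laboratory tests.** The last liver, renal and pregnancy tests are also at visit 6. Adverse event monitoring does continue to visit 8.
- **Outcomes read in follow-up.** The Dysmenorrhea subsection compares the groups on NRS and VMSS by time point, including 4 and 8 weeks after treatment. Table 1 also records the acne NRS at weeks 12 and 16. These readings are meant to describe participants who are off treatment.

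**Working it through.** **Inputs**

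- Pouches per day: 3 (GBH and DJS section; Placebo section).
- Treatment period: 8 weeks = 8 × 7 = 56 days (same sections; abstract).
- Pouches per supply: 45 (Placebo section).
- Dispensing visits in the text: 2, 3, 4, 5, 6 = 5 supplies.
- Dispensing visits in Table 1: 2, 3, 4, 5 = 4 supplies.

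**Step 1: need over the stated period.** Pouches needed = pouches per day × days = 3 × 56 = 168.

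**Step 2: is 45 per supply consistent with two-weekly visits?** Two weeks need 3 × 14 = 42, so 45 leaves 3 spare, or one day. The size of each supply is sound. Only the number of supplies is in question.

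**Step 3: total supply under each list.** Pouches = 45 × supplies; days covered = pouches / 3; surplus = pouches − 168.

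| Source | Supplies | Pouches | Days covered | Surplus over 168 |
|---|---|---|---|---|
| Table 1 | 4 | 180 | 60 | 12 pouches (4 days) |
| Placebo section, as written | 5 | 225 | 75 | 57 pouches (19 days) |

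**Step 4: size of the contradiction.** 225 − 180 = 45 pouches; 45 / 3 = 15 days. The 4-day surplus exists under either list and is not part of the contradiction. The disputed amount is therefore 15 days, not 19.

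**Step 5: effect on follow-up, if the visit 6 supply were taken.** Assume visits on their nominal days and dosing at three a day without a break from week 8.

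- Last dose as stated: about day 56. Gap to week 12 (day 84): 84 − 56 = 28 days.
- Last dose with the extra 15 days: about day 56 + 15 = 71. Gap to week 12: 84 − 71 = 13 days.
- Gap to week 16 (day 112): 112 − 71 = 41 days, against 112 − 56 = 56.

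**Step 6: what is out of reach.** The primary outcome runs from baseline to the end of treatment at week 8, so product issued at week 8 cannot influence it. The same holds for the lesion counts, the global assessment and the week 8 NRS and VMSS comparisons.

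**The case against.** The strongest reply is that the range from visit 2 to visit 6 describes the span the supplies cover, not the visits at which they are handed out. Much supports this reading. Eight weeks at two-weekly intervals is four intervals. The treatment duration is the same wherever it is given. In Table 1, product at visits 2 to 5 pairs with compliance checks at visits 3 to 6, so each supply is checked one visit later. On this reading the conflict is a loose phrase.

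The reading is plausible, but it does not remove the conflict. The sentence says that product is provided at those visits, and it names the last visit with its week. A literal reader would dispense at visit 6, and the table says otherwise.

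The reply does succeed in limiting the consequences. A reader might infer more than the documents support in three ways:

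- **That follow-up is contaminated.** Holding product is not taking it. Nothing tells participants to dose after week 8, and every dosing statement stops there. The shorter gap before week 12 arises only if the supply is used contrary to the stated duration.
- **That fully adherent participants would fall below the 80% threshold.** This would need pouches dispensed as the denominator. The Per-protocol population section requires that patients "consume more than 80% of the prescribed doses of the study drug", and the withdrawal criteria also refer to prescribed doses. Three a day for 8 weeks is 168 under either list, so a participant who takes them all scores 168/168 = 100%.
- **That the ±3-day visit windows add to the problem.** Any strain they put on a 45-pouch supply arises equally under both lists, so it is a separate matter.

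**Conclusion.** The point holds as an inconsistency between text and table in an operational rule. As written, the Placebo section conflicts with Table 1 and provides more product than the stated 8 weeks can use. Its size is one supply of 45 pouches, or 15 days, at the visit that ends treatment and closes compliance checks and laboratory testing.

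The possible harm is confined to the follow-up readings: dysmenorrhea NRS, VMSS and acne NRS at weeks 12 and 16. The gap from last dose to the week 12 reading would shrink from 28 days to about 13. That figure assumes nominal visit days, three pouches a day, and use of the visit 6 supply against the stated duration. The documents do not say that this would happen. The week 8 primary endpoint and the per-protocol rule stand as they are. This is worth correcting because the correction is cheap and sites need one rule, not because the main result is at risk.

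**What to change.** Reconcile the dispensing sentence in the Placebo section, the product row of Table 1 and the 8-week treatment period, so that they give one list of dispensing visits and one total number of pouches per participant. The sponsor should say which list is intended; this review does not choose between them.

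The cost is one sentence or one table cell, plus a check that the sites' dispensing instructions agree with it. No new data, participants or analyses are needed.
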